### Outcomes

The primary outcome measure is a risk factor for early pension, measured by the screening questionnaire SIBAR, a score ≤8 indicating a decreased risk for premature pension. The primary endpoint will be the assessment at the end of the internet-based treatment (T2, that is, 3 months after inpatient rehabilitation). Secondary outcome measures include the subjective prognosis for work and capability, also measured by the SIBAR, and scales for the work-related behavior and experience pattern (AVEM-44 [45]), physical and mental health (Patient Health Questionnaire [47], Generalized Anxiety Disorder 7-item Scale [48], Short-Form 12-item Health Survey [49]), social support (Berlin Social Support Scale [50]), therapeutic alliance (Helping Alliance Questionnaire [51], Helping Alliance Questionnaire II [52]) and self-developed items measuring patients‘ satisfaction with the aftercare program. Long-term effects of the primary outcome measure will be analyzed 9 months after termination of the internet-based aftercare at T3. Except for the Helping Alliance Questionnaires, only applied in the intervention group, all instruments are used in both randomized arms.

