### Statistical methods

For the primary analyses, analysis of covariance will be used to compare SIBAR risk scores 12 weeks after the discharge of inpatient rehabilitation (T2) between the internet-based aftercare program (intervention group) and the control group, with covariates for rehabilitation clinic and baseline SIBAR risk score (T1). Cohen’s effect sizes will be calculated. Intention to treat analyses as well as completer analyses will be conducted. Replacement strategies of missing values will be discussed after assessing the pattern of the missing value structure.

For the secondary analyses, self-report questionnaires (AVEM-44; Patient Health Questionnaire; Generalized Anxiety Disorder 7-item Scale; Short-Form 12-item Health Survey; Berlin Social Support Scale; Helping Alliance Questionnaire) will be analyzed by mixed models with repeated measurements. It is expected that the SIBAR risk score and the other self-report measures will not be linear across time. Therefore, these measures will be evaluated by a linear model with fixed effects for treatment and rehabilitation center and time. There will be an indicator variable for the post treatment measurements and the SIBAR risk score at baseline will serve as a covariate. All analyses will be conducted on a two-sided level of significance of α = 0.05.

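### For the two-arm secondary scales other than SIBAR, the stated model names only baseline SIBAR as baseline covariate and only a treatment main effect; the Helping Alliance Questionnaire cannot be in a between-arm model at all

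*Protocol article*

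**What the plan says.** All of this is in the protocol article, under Statistical methods unless noted.

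- The secondary scales (AVEM-44, PHQ, GAD-7, SF-12, Berlin Social Support Scale, Helping Alliance Questionnaire) "will be analyzed by mixed models with repeated measurements".
- The model is motivated jointly for SIBAR and the other scales: "It is expected that the SIBAR risk score and the other self-report measures will not be linear across time".
- Its fixed part is then listed: "these measures will be evaluated by a linear model with fixed effects for treatment and rehabilitation center and time". No treatment-by-time term is named.
- The next sentence adds two elements: "There will be an indicator variable for the post treatment measurements", and "the SIBAR risk score at baseline will serve as a covariate". No other baseline covariate appears.
- The primary analysis, by contrast, is an analysis of covariance of SIBAR at T2 with clinic and SIBAR at T1 as covariates, so there the outcome is adjusted for its own baseline.
- The list of modelled scales ends with "Berlin Social Support Scale; Helping Alliance Questionnaire", while the Outcomes section states: "Except for the Helping Alliance Questionnaires, only applied in the intervention group, all instruments are used in both randomized arms". The legend of Figure 1 carries the same restriction.

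**The concern.** A scale's own pre-treatment score is usually the best single predictor of its later score. SIBAR covers risk of early retirement, occupational stress and subjective need for occupational treatment. It may predict later anxiety, depression or social support to some degree, but there is no reason to prefer it to the earlier score on the same scale. Using it alone gives up precision and leaves chance differences in the outcome's own baseline in the estimate.

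The own baseline can also enter a repeated-measures model as an outcome row. The treatment effect must then be allowed to differ before and after aftercare, and the listed terms do not provide for that.

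A separate point is that a model with a treatment effect has been assigned to a questionnaire that exists in one arm only.

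**Working it through.** **Inputs.** The article gives no figure for the secondary analyses and no correlations between measurements. From Sample size calculation: mean cluster size 6, intracluster correlation 0.30, dropout 40% of 800, d = 0.30, power 0.80, alpha 0.05. The steps used here reproduce: design effect 1 + 5 × 0.30 = 2.5; analysed patients 800 × 0.6 = 480; effective number 480/2.5 = 192. The base figure of 190 is not used.

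Assumed: correlation of outcome with own baseline r_own = 0.5 to 0.7, and with baseline SIBAR r_S = 0.1 to 0.4. Adjustment is taken to reduce variance within and between clusters alike.

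**Reading A: only post-treatment values are outcome rows.** At one visit, variance after adjustment is proportional to 1 − r². The ratio for SIBAR against own baseline is (1 − r_S²)/(1 − r_own²).

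| r_own | r_S | Variance ratio | Standard error |
|---|---|---|---|
| 0.5 | 0.4 | 0.84/0.75 = 1.12 | +6% |
| 0.6 | 0.3 | 0.91/0.64 = 1.42 | +19% |
| 0.7 | 0.1 | 0.99/0.51 = 1.94 | +39% |

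To illustrate, at effective N 192 and d = 0.30 (the planning value for the primary outcome), power is about 0.55 to 0.62 with SIBAR and 0.67 to 0.83 with own baseline.

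*Imbalance.* Take an own-baseline difference of 0.10 SD, SIBAR balanced, and a correlation of 0.4 between the two baselines (assumed). The part left in the estimate is 0.10 × (r_own − 0.4 r_S)/(1 − 0.4²). For r_own = 0.5, r_S = 0.4 this is 0.10 × 0.34/0.84 = 0.04 SD. For r_own = 0.7, r_S = 0.2 it is 0.10 × 0.62/0.84 = 0.07 SD. If the planned intracluster correlation also held at baseline, the SD of the between-arm baseline difference would be 2/√192 = 0.14, so a gap of 0.10 SD or more would occur in roughly half of such trials.

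**Reading B: T1, T2 and T3 are all outcome rows.** Assume equal variances and a common correlation r between visits. With treatment as a main effect only, the three visits receive equal weight. A true pattern of (0, δ, δ) is then estimated as (0 + δ + δ)/3 = 2δ/3.

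Relative variance of the estimate, mean of T2 and T3 unless noted:

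| Model | r = 0.5 | r = 0.6 | r = 0.7 |
|---|---|---|---|
| Treatment main effect only, T1 a row (estimates 2δ/3) | 0.67 | 0.73 | 0.80 |
| Post rows only, no baseline | 0.75 | 0.80 | 0.85 |
| Post rows only, SIBAR covariate (r_S = 0.3) | 0.66 | 0.71 | 0.76 |
| T1 a row, treatment-by-post term | 0.75 | 0.60 | 0.45 |
| T1 a row, baseline means constrained equal | 0.50 | 0.44 | 0.36 |

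The smaller variance in the first row does not make up for the shrinkage. At r = 0.5 the effect over its standard error is 0.667/√0.667 = 0.82, against 1/√0.75 = 1.15 for post rows only, both without a covariate.

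**Helping Alliance Questionnaire.** Every patient with data is in the intervention arm, so the treatment column is constant and cannot be separated from the intercept. No between-arm contrast exists, whatever covariate is chosen.

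**The case against.** The strongest reply is that the covariate clause is half of a sentence whose other half introduces the post-treatment indicator. An indicator of that kind most naturally separates post- from pre-treatment rows, and the model is called a repeated-measures model. On that reading each scale's own T1 value is already in the analysis. With baseline means constrained equal, the loss disappears. With an unconstrained treatment-by-post term it mostly does, although at r = 0.5 the variance (0.75) is still above that of post rows with SIBAR (0.66).

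This stands as far as it goes: a reader might infer that the loss of precision is certain, and the article does not support that. Nor does it establish the rescuing model. Neither an interaction nor a baseline constraint is stated. The model also covers SIBAR itself, which would make baseline SIBAR both an outcome row and a covariate, and this speaks for post rows only.

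Other stronger readings also fail:

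- **All secondary analyses are affected.** For SIBAR, including its long-term analysis at T3, the covariate is its own baseline.
- **The estimates are biased by imbalance.** Under randomisation the post-only estimate is unbiased in expectation, and its standard error already reflects chance imbalance. What is lost is the chance to adjust for it.
- **A ratio of 1.42 means losing about 30% of patients** (1 − 1/1.42). That holds only if whole clusters are lost. Thinning each cluster from 6 to 4.2 moves the relative variance from 2.5/6 = 0.417 to (1 + 3.2 × 0.30)/4.2 = 0.467, a ratio of 1.12.
- **The one-arm questionnaire adds to the loss of precision.** It does not. It is an error in the list, and no wrong estimate can result because none can be computed.

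**Conclusion.** The point holds for AVEM-44, PHQ, GAD-7, SF-12 and the Berlin Social Support Scale. The wording leaves two readings, and both need a change:

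- **Post-treatment rows only:** the standard error is about 6% to 39% larger than with own-baseline adjustment, and chance imbalance in the outcome's own baseline is not adjusted for. The range is for a single visit and rests wholly on the assumed correlations.
- **T1 as an outcome row:** a constant post-treatment effect is estimated at about 2/3 of its size. This assumes three rows per patient (T1, T2, T3) and a common correlation. Unlike the first case, it is a systematic shrinkage.

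The inclusion of the Helping Alliance Questionnaire contradicts the Outcomes section and needs no assumption. The primary analysis is untouched by any of this. The matter deserves correction before analysis but concerns secondary outcomes only.

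**What to change.** 1. State which visits are outcome rows in the secondary model.
2. Then choose one form for every two-arm scale:
   - T2 and T3 as outcomes, with the scale's own T1 score as covariate and baseline SIBAR optional in addition; or
   - T1, T2 and T3 as outcomes, with a treatment-by-time term and baseline means constrained equal between arms.
3. Take the Helping Alliance Questionnaire out of the between-arm list and analyse it within the intervention arm.

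The cost is a change of wording, with no new data and no new patients. It assumes that the two-arm scales are collected at T1. The Interventions and Assessment sections mention a baseline questionnaire and feedback on AVEM-44 change over time, but the figure with the full schedule is not shown. A scale that turns out to be measured only at T0 would use its T0 score.

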### Ethical issues

The study protocol and the final version of the written informed consent form were approved by the Ethics Committee of the Federal State of Rhineland Palatinate (Germany), which is responsible for the Principal Investigator (Ref. No. 837.415.10[7424]) and by the ethics committees responsible for the cooperating rehabilitation clinics.

The procedures set out in this protocol pertaining to the conduct, evaluation and documentation of this trial were designed to ensure that all persons involved in the trial abide by Good Clinical Practice and the ethical principles described in the current revision of the Declaration of Helsinki. The trial will be carried out in keeping with local legal and regulatory requirements.

Before being admitted to the clinical trial, patients must consent to participate after the nature, scope and possible consequences of the clinical trial have been explained in a form understandable to them. The patients must give written informed consent to participate in the study, including their consent to publish.

We expect a very low risk for adverse events. Nevertheless, participants have the possibility to contact the staff at the study center via e-mail or on a mobile help number with the guarantee of a response during working hours (8.00 a.m. to 5.00 p.m.) on weekdays. On weekends and at all other times, patients are referred to a Germany-wide crisis telephone number, which is indicated on our internet platform. All adverse events reported by the participants or detected by the online therapist or respective study staff will be collected during the trial and must be documented in the case report form. The clinical course of the adverse event will be followed by the principal investigators ([name], RZ), who will contact the participants in case of a crisis for further diagnostics via telephone or for necessary referrals to practitioners near the participant.

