In two of the four rehabilitation centers, patients of both randomized arms have the opportunity to log on to the study website during their inpatient rehabilitation treatment and complete the baseline questionnaire online. In the other two clinics without sufficient technical equipment, the participants get the same questionnaire on a paper-pencil basis and are prepared for their first login at home by the trainer. In any case, every participant gets a sealed envelope including the personal access data and a written description of the intervention or control program. After login, all patients are asked to change their password, to choose a nickname and to enter their e-mail address if they want to be informed by automated e-mails about study-related information, therapeutic tasks and questionnaires to be filled out.

The essential component of the online aftercare program for the intervention group is a standardized weekly writing task (‘blog’) followed by individual feedback from the online therapist within one week day, both only visible to the individual patient and the online therapist. Further online features for the intervention group are a self-test with computer-generated feedback to the participants’ individual ‘Arbeitsbezogenes Verhaltens und Erlebensmuster’, Kurzform 44 (Pattern of Work-related Coping Behavior, short-form 44; AVEM-44 [45]) and its change over time, audio samples with progressive muscle relaxation exercises [46], the GSA worksheets and a moderated patient forum. All these features are accessible for 12 weeks. The internet-based therapeutic interventions are performed by two trained psychologists with regular supervision. With the participants’ consent, all blog contacts between therapist and patient are fully documented in the database, allowing subsequent comparisons and analyses concerning the contents.

The control group receives regular e-mail reminders to use selected and online-deposited information about stress management and coping (physical activity, relaxation, healthy diet and sleep hygiene) over the same period of time. All information is permanently downloadable for participants of the control group for the duration of 12 weeks. Overall there are six e-mail reminders, that is, one every fortnight, beginning with a universal reminder, followed by reminders for the five specific topics on stress management and coping.

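### Detection of adverse events by the online therapist is possible in the intervention arm only, so event counts recorded up to T2 are not like for like between the arms

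*Protocol article*

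**What the plan says.** The rule for capturing harms stands under Ethical issues in the protocol article: "All adverse events reported by the participants or detected by the online therapist or respective study staff will be collected during the trial". It names three routes: the participant, the online therapist and study staff. The same section adds that "participants have the possibility to contact the staff at the study center via e-mail or on a mobile help number", with a response during weekday working hours and a national crisis line at other times. Neither is restricted to one arm. The section expects adverse events to be very uncommon and gives no rate.

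What the online therapist can observe follows from the Interventions section. "The essential component of the online aftercare program for the intervention group is a standardized weekly writing task", answered individually by the therapist; text and reply are "both only visible to the individual patient and the online therapist". The list of further intervention-group features ends with "the GSA worksheets and a moderated patient forum". Of the whole set the article says "All these features are accessible for 12 weeks".

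For the other arm it says: "The control group receives regular e-mail reminders to use selected and online-deposited information about stress management and coping". The number of messages is fixed: "Overall there are six e-mail reminders, that is, one every fortnight". The section describes no therapist and no scheduled staff contact for control patients over these weeks.

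**The concern.** One of the three named routes works in one arm only. During the 12 aftercare weeks a therapist reads what an intervention patient writes and may notice a deterioration that the patient would never have reported as an adverse event. Nobody is described as reading anything from a control patient, whose event becomes known mainly if the patient makes contact.

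Two things are at stake. The first is interpretation: the intervention asks vocationally strained patients to write every week about difficulties at work, so readers will want to know whether some of them got worse. A modest surplus of recorded events in that arm could reflect harm or closer observation, and the counts alone would not show which. The second is recognition: the investigators' follow-up of an event begins only once the event is known, so an unreported control event may receive none.

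**Working it through.** The article gives no adverse-event figure to reproduce. The check sets the routes side by side and then illustrates the possible size.

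**Routes by arm, from discharge (T1) to T2**

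| Route | Intervention | Control | Source |
|---|---|---|---|
| Patient contacts the study centre | yes | yes | Ethical issues |
| Weekly text read by the therapist | yes, up to about 12 | no | Interventions |
| Moderated forum | yes | no | Interventions |
| Study staff | named, no scheduled contact described | named, no scheduled contact described | Ethical issues; Interventions |
| Fortnightly e-mail | not described | 6, outgoing reminders | Interventions |
| T2 questionnaire | yes | yes | Assessment; Outcomes; not named as a source of adverse events |

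Before the second part of the fourth inpatient session the arms are handled alike. After the 12 weeks the therapist features end, so from T2 to T3 the named routes are the same in both arms. The imbalance is confined to the aftercare period.

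**Direction.** Let s be the probability that an event is detected by the routes open to both arms, and t the probability that the therapist detects an event that those routes would miss. Then:

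- control detection = s
- intervention detection = s + (1 − s) × t
- ratio of recorded events at equal true risk = 1 + t × (1 − s) / s

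The ratio exceeds 1 whenever t > 0 and s < 1. This takes s to be the same in both arms.

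**Size, illustration only.** Recorded events = 400 × true risk × detection probability. The 400 per arm comes from the Abstract. The true risks and all detection rates are assumptions, because the article gives none. Intervention detection is held at 80%.

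| True risk, both arms | True events per arm | Recorded, intervention (80%) | Recorded, control (60%) | Recorded, control (40%) | Recorded, control (20%) |
|---|---|---|---|---|---|
| 2% | 8 | 6.4 | 4.8 | 3.2 | 1.6 |
| 5% | 20 | 16 | 12 | 8 | 4 |
| 10% | 40 | 32 | 24 | 16 | 8 |
| Spurious ratio | | | 0.8/0.6 = 1.33 | 0.8/0.4 = 2.0 | 0.8/0.2 = 4.0 |

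The ratio does not depend on the true risk. With equal detection (80% in both arms) it is 1.0. An intervention rate of 80% presumes that patients keep writing. The Sample size calculation section allows for 40% dropout, and patients who stop writing would pull the ratio towards 1.

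**The case against.** The strongest reply is that no planned analysis is damaged. Adverse events appear neither under Outcomes nor under Statistical methods. The sentence stands in an ethics section and serves collection and follow-up. That is correct, and the efficacy analysis is untouched. Even so, if event counts are published by arm, readers will compare them.

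A second reply is that an article condenses the full protocol, and the case report form or the questionnaires may already contain a standard enquiry. That is possible. The point therefore rests on what the article does state, a set of routes that differ by arm, and not on missing detail. If a common enquiry exists, the remedy is largely in place and only needs to be named as the basis for comparison.

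Third, study staff are a named route not limited by arm, and all patients can reach the study centre. Control patients are therefore not without a channel. But one channel depends on the patient's initiative, and no scheduled contact is described through which the other would work during aftercare.

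Three stronger readings are tempting and are not supported:

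- A reader might infer that harm from the writing task could not be recognised at all. The Patient Health Questionnaire, the Generalized Anxiety Disorder scale and the Short-Form 12 are used in both arms and analysed with repeated measurements, so average psychological worsening is measured in the same way in each. They do not capture discrete events.
- A reader might take the fourfold figure as the expected excess. It is one end of an assumed range.
- A reader might infer unequal capture up to T3, or that crisis follow-up goes mostly to intervention patients. The named routes are the same in both arms after T2, and the article gives no figure for the second claim.

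**Conclusion.** The concern holds in a limited form. The stated rule gives the intervention arm a route of detection that the control arm lacks during the 12 aftercare weeks, and nothing else described offsets it. Event counts recorded up to T2 are therefore likely to be higher in the intervention arm at equal true risk, and an unreported event or crisis in a control patient may be missed. The direction follows from the design, provided that the shared routes work equally in both arms. The size cannot be derived from the document: about 1.3 to 4 under assumed detection of 80% against 60% down to 20%, and nearer to 1 if few patients write. The gap concerns discrete events and neither average symptom change nor the primary analysis.

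**What to change.** Put the same short adverse-event item into the T2 and T3 questionnaires of both arms, online and on paper, asking about new or worsened health or psychological problems, hospital admission or crisis since the last questionnaire. Base any between-arm description of harms on this item. Report therapist-detected events separately, and state that this route existed in one arm only.

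Timing limits what can be done. Trial status expects the last follow-up by September 2013. With T3 at 12 months after T1, the last T1 falls around September 2012 and the last T2, 3 months later, around December 2012, before publication in January 2013. If T2 is complete, the item can go only into the remaining T3 assessments. It would then cover part of the sample, and patients would have to recall the aftercare period. Separate reporting and the statement on ascertainment remain possible at any stage.

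The cost is one or two items added to an assessment of about 45 minutes, and more reports for the study centre to document through its existing process.
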